### Secondary Outcomes

Subsequent pregnancy within 2 years.Recurrent cesarean scar pregnancy in a subsequent pregnancy.Complications in a subsequent pregnancy.Subsequent infertility including cesarean scar niche.Association of above outcomes and the treatment option.

### Trial Discontinuation

All the patients will be withdrawn from the trial upon participant’s request at any time point and there will be no allowance for participating in this trial.

### Statistical Analysis

All the data will be expressed as mean and SD. Student t-test or ANOVA will be performed when appropriate using Prism software version 8.4. Two side p value of less than 0.05 will be considered statistically significant.

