### Participants

#### Sample Size Calculation

The sample size calculation was based on the reduction of the proportion of cases who lost more than 300 ml of blood during operation. Our recent study (15) showed intraoperative blood loss with a mean of 184 ml and a standard deviation (SD) of 313 ml. Converting to a Z-score, about 35% of cases would have more than 300 ml of intraoperative blood loss. With 90% power at the 5% significance level, recruiting 200 cases in total, we will be able to detect a difference of 20% between two groups.

Therefore, in this randomized clinical trial, 200 women newly diagnosed with cesarean scar pregnancy will be recruited within three years and equally divided into two groups.

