### Primary Outcomes

Comparisons of duration of operation, intraoperative blood loss and intraoperative complications between treatments by ultrasound guided suction curettage with or without UAE.The numbers of cases that receive emergency hysteroscopic and/or laparoscopic resection.Retrospectively analyze the intraoperative blood loss, taking into account the subtypes of cesarean scar pregnancy.Retrospectively validate the QRS score to predict intraoperative blood loss.

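### Mean and SD for all data does not suit the yes/no outcomes or the skewed blood loss, and the proportion that sizes the trial has no matching analysis

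*Protocol article*

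**What the plan says.** The Statistical Analysis section of the protocol article has three sentences of substance. On summaries and tests: "All the data will be expressed as mean and SD. Student t-test or ANOVA will be performed when appropriate". On the threshold: "Two side p value of less than 0.05 will be considered statistically significant".

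The outcomes it must serve are mixed. Under Primary Outcomes, duration of operation and blood loss are continuous, but intraoperative complications are yes/no, and a further item is a count of patients: "The numbers of cases that receive emergency hysteroscopic and/or laparoscopic resection". Under Secondary Outcomes, most items are yes/no per woman, for example "Recurrent cesarean scar pregnancy in a subsequent pregnancy".

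The Sample Size Calculation section uses a proportion; it is "based on the reduction of the proportion of cases who lost more than 300 ml of blood during operation". Its input is "intraoperative blood loss with a mean of 184 ml and a standard deviation (SD) of 313 ml".

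**The concern.** The summary rule covers all data without exception, so this is stated text and not merely detail left to another document. Read literally, it reports a count of emergency resections as a mean with an SD, and blood loss with an SD far larger than its mean.

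The trial asks whether embolization is needed to control bleeding. Its readers will want to know how many women in each arm bled heavily or needed emergency resection, how large the difference is and how precisely it is estimated, and what a typical woman lost. The stated summary gives none of these clearly. The comparison for which 200 women are recruited is not named among the analyses. For rare events, where the choice of test can move a result across 0.05, the choice is not fixed in the text.

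**Working it through.** **1. The trial is sized on a proportion.** Inputs from the Sample Size Calculation section: mean 184 ml, SD 313 ml, cut-off 300 ml, 90% power, 5% significance, a 20-point difference, 200 women in two equal groups.

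- Event rate by the article's own normal conversion: z = (300 − 184)/313 = 0.371, and 1 − Φ(0.371) = 35.5%, which matches the stated 35%.
- Two-proportion formula, 35% v 15%, two-sided, pooled variance under the null: n = [1.960·√(2·0.25·0.75) + 1.282·√(0.35·0.65 + 0.15·0.85)]² / 0.20² = (1.200 + 0.764)² / 0.04 ≈ 96.4, so 97 per arm or 194 in total. Power at 100 per arm is 91.0%.

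The stated 200 therefore reproduces as a comparison of two proportions, which the Statistical Analysis section does not name. If the arms showed exactly 35% and 15%, the natural report would be a risk difference of 20 points with SE √[(0.2275 + 0.1275)/100] = 0.0596 and 95% CI 0.20 ± 1.96·0.0596, or 8.3 to 31.7 points.

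**2. Mean and SD for yes/no data.** For 4 events in 100, the mean is 0.04 and the SD is √(0.04·0.96·100/99) = 0.197. The SD is determined by the mean and n, so it adds nothing, and the pair hides the count.

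**3. Mean and SD for blood loss.** SD/mean = 313/184 = 1.70. Mean minus SD is −129 ml. A normal curve with these values puts Φ(−184/313) = 27.8% of women below zero, so the distribution must be strongly skewed. The documents give no shape; under two assumed shapes with the same mean and SD:

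- Lognormal: median = 184/√(1 + 1.70²) ≈ 93 ml.
- Gamma (shape (184/313)² = 0.346, scale 313²/184 = 532 ml): median ≈ 55 ml.

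The mean of 184 ml is then about 2 to 3.3 times the median.

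**4. Does the t-test give invalid p-values?** Two-sided type I error on 0/1 data, 100 per arm, by exact binomial enumeration:

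| Event rate | t-test | Uncorrected chi-square | Fisher exact |
|---|---|---|---|
| 35% | 4.8% | 5.0% | 3.4% |
| 10% | 5.2% | 5.2% | 2.9% |
| 5% | 4.4% | 4.4% | 2.1% |
| 2% | 4.0% | 4.0% | 0.5% |

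For raw blood loss (40,000 simulated trials), the t-test's type I error is 4.3% under the lognormal and 4.8% under the gamma. The test holds its level in both settings.

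**5. Sparse events, 100 per arm.** The event counts are hypothetical; the documents give no emergency-resection rate.

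| Events | t-test | Uncorrected chi-square | Fisher exact |
|---|---|---|---|
| 0 v 4 | 0.0436 | 0.0434 | 0.121 |
| 0 v 5 | 0.0235 | 0.0235 | 0.059 |
| 1 v 7 | 0.0304 | 0.0304 | 0.065 |

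For 0 v 4: t = 0.04/√[(0.0384·100/198)·(2/100)] = 2.03; chi-square z = 0.04/√(0.02·0.98·2/100) = 2.02; Fisher p = 2·C(100,4)/C(200,4) = 0.121. The expected event count per arm is 2, 2.5 and 4 in the three rows. All lie below the conventional limit of 5, at which many analysts would switch to Fisher.

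**6. Power for blood loss in ml.** For a halving, t-test v rank test: 86% v 98% under the lognormal, 80% v 54% under the gamma. The ranking depends on the assumed shape.

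**The case against.** The strongest reply has three parts.

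The tests, unlike the summary, are limited to cases where they are appropriate. Nothing orders a t-test on complications or recurrence, and a condensed article commonly leaves the test for a yes/no outcome to a fuller document. This stands as far as it goes: a reader might infer that a t-test or ANOVA is prescribed for every outcome, and the text does not say so. It does not rescue the summary rule, which has no such qualifier, or explain why the only named tests leave out the comparison that sizes the trial.

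A reader might also infer that the plan will produce wrong p-values. The figures do not support that. At 100 per arm the t-test on 0/1 data is almost the same test as the uncorrected chi-square, and the gap to Fisher mainly reflects Fisher's conservatism. The raw t-test on blood loss also holds its level. In small, unequal subsets it can do worse: at an assumed 10 v 40 women and event rates of 2 to 5%, its type I error is 7.8 to 8.8%, while at 20 v 20 it is at most 1.2%. The documents give no subset sizes, so no conclusion rests on this.

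Finally, comparing mean millilitres lost is defensible. A log-scale model changes the target to a ratio of geometric means and needs a rule for zero losses, and a power gain from log or rank methods is not assured. This stands in full.

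**Conclusion.** The point holds as one of summary and specification, of moderate weight. A mean-and-SD rule for all data does not suit two of the primary outcomes, most of the secondary outcomes, or blood loss with an SD 1.7 times its mean. The proportion above 300 ml, which yields the 200, has no matching analysis. The consequences are misleading summaries, no stated risk difference with its interval, and a choice of test for sparse events that is open enough to decide significance (0 v 4: 0.044 or 0.12). Invalid inference in the main two-arm comparison is not among them.

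The SD-to-mean ratio and the reproduced sample size come from the article's own figures. The medians of 93 and 55 ml rest on assumed shapes, and the sparse-event counts are illustrations.

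**What to change.** Rewrite the Statistical Analysis paragraph:

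- **Yes/no outcomes**, including blood loss above 300 ml, complications, emergency resection and the yes/no secondary outcomes: n (%) per arm and risk difference with 95% CI. Test by chi-square, or by Fisher exact when expected counts are small, with the limit stated in advance.
- **Blood loss in ml and operation time:** median (IQR) alongside mean and SD. The t-test on means may stay.
- **Optional:** a log-scale or rank-based analysis of blood loss as a prespecified sensitivity analysis, not as a replacement.

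The sample size does not change because of this, since 200 already rests on two proportions. At 35% v 15% with 100 per arm, exact power is 91.4% by chi-square and 88.5% even if Fisher were used. The cost is one rewritten paragraph and a somewhat more conservative test where events are sparse. It should be settled before outcome data are seen by arm, so that the test is not chosen after the result.

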Pre-assessment of blood loss is very important to gynecologists. Our recent study reported that gestational age of cesarean scar pregnancy and blood flow around the site of the gestational sac detected by ultrasound are risk factors for potential intraoperative blood loss (13). We then developed a risk-scoring system (**Table 1**) to estimate intraoperative blood loss, and we found that women with a total score higher than three have a risk for intraoperative blood loss (13). A previous study also used a color Doppler scoring system to estimate intraoperative blood loss, according to vascularization of the pregnancy, and it indicated that women with a higher score have a higher risk of intraoperative blood loss (12).

**Table 1 T1:** Risk-scoring system for the prediction of compression hemostasis requirement.

Variable	Score
Vascularity around the gestational sac*	
No obvious blood flow	0
Sparse or sporadic blood flow	1
Vessel looks like short-columnar pattern	2
Vessel looks cord-like pattern	3
Massive blood flow or arteriovenous fistula	4
Pregnancy duration	
≤40 days	0
41–50 days	1
>50 days	2

*As demonstrated on a color Doppler ultrasonography.

There is currently no randomized clinical trial to compare the intraoperative blood loss and postoperative outcomes by surgical treatment such as ultrasound guided curettage with or without UAE in women with cesarean scar pregnancy. Therefore, we will run a randomized clinical trial to primarily investigate whether UAE is overused in controlling intraoperative blood loss in clinical practice. We recently established a risk-scoring system (QRS) to estimate intraoperative blood loss (13), and we will then retrospectively validate the role of QRS in estimating intraoperative blood loss in this randomized clinical trial with a relatively large sample size. Recently a number of studies reported potential complications in a subsequent pregnancy in women who received surgical treatment (14). Whether the complications in a subsequent pregnancy are related to the options of the previous treatment is unknown. Therefore, the secondary measurement of this randomized clinical trial is to follow up the outcomes in a subsequent pregnancy in women treated by ultrasound guided curettage with or without UAE.

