## Discussion

Interventions for cesarean scar pregnancy could cause a massive intraoperative blood loss due to the highly vascular nature of the site of pregnancy. This consequently results in using UAE as one of the options to prevent intraoperative blood loss in clinical practice. However, a recent retrospective study suggested that UAE may be overused in clinical practice (11). Therefore, in this randomized clinical trial, we primarily aim to evaluate the necessity of UAE as a treatment option for cesarean scar pregnancy in order to control the intraoperative blood loss. We will then retrospectively take into account the subtypes of cesarean scar pregnancy to understand whether the optimal options are dependent on the subtypes of cesarean scar pregnancy.

Pre-assessment on predicting intraoperative blood loss which may be dependent on the size and/or site of the sac and the gestational age will help gynecologists select an optimal option for cesarean scar pregnancy treatment. A recent retrospective study used crossover sign (COS) to predict blood loss in surgical treatment (17), suggesting that the crossover sign (COS) is an independent risk factor for severe blood loss during treatment of cesarean scar pregnancy (18). We also recently developed a risk-scoring system (QRS) to estimate blood loss during surgical treatment with a 93.8% sensitivity and 6.3% false negative (13), which has some similarities with the COS system. Due to the relatively small sample size in our previous study, therefore, in this randomized clinical trial with a relatively large sample size, we will retrospectively validate the role of the QRS score in estimating intraoperative blood loss. We hope that this study will generate sufficient evidence for optimal cesarean scar pregnancy treatment. If effective, we believe the QRS score can be a cost-effective and safe tool to estimate intraoperative blood loss in order to reduce the unnecessary use of UAE in clinical practice.

In addition, whether recurrent cesarean scar pregnancy and the outcomes in a subsequent pregnancy including complications,and subsequent fertility in women treated for cesarean scar pregnancy are associated with their previous treatment has not been described well in literature. We hope that the secondary outcomes of the study can provide some useful information on the outcomes of a subsequent pregnancy.

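### Validating the QRS is a primary outcome, but the only analyses named compare means and cannot estimate the score's sensitivity

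*Protocol article*

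**What the plan says.** Under Primary Outcomes, the protocol article includes the item "Retrospectively validate the QRS score to predict intraoperative blood loss". The Introduction gives the cut-off: "women with a total score higher than three have a risk for intraoperative blood loss". The Abstract and the Discussion report the score's earlier performance, in the Discussion's words "with a 93.8% sensitivity and 6.3% false negative". The Discussion adds that the earlier study was fairly small, that this larger trial will validate the score, and that an effective score could be a safe way to cut unnecessary UAE.

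The Statistical Analysis section has three sentences. The first is "All the data will be expressed as mean and SD", the second is "Student t-test or ANOVA will be performed when appropriate using Prism software version 8.4", and the third is "Two side p value of less than 0.05 will be considered statistically significant". None of them mentions the QRS. Sensitivity, specificity, ROC analysis, confidence intervals and a rule for calling the score validated are not mentioned anywhere as planned analyses.

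Two further places bear on the reference event. The title of Table 1 says that the score predicts the need for compression hemostasis. The Sample Size Calculation uses blood loss above 300 ml.

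**The concern.** The score's cited performance is a classification property: the share of women with the bleeding event whom the cut-off flags. A t-test or ANOVA of blood loss across score groups has a different null hypothesis, namely equal mean loss. Rejecting it shows that the score is associated with blood loss. It does not show how many heavy bleeders fall in the low-score group. The problem is the hypothesis tested, not the shape of the data, because a rank test of the same comparison would leave the same gap.

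The stated use is to decide who can go without UAE. The safety of that use depends on missed heavy bleeders (sensitivity and negative predictive value). The number of UAEs that could be avoided depends on specificity. The named analysis estimates none of these. The two performance figures given, 93.8% and 6.3%, are complements (up to rounding) and carry one piece of information. No specificity is given.

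**Working it through.** **Inputs from the protocol article.** Mean blood loss 184 ml, SD 313 ml, threshold 300 ml, 200 women in two equal arms, 35% above 300 ml and a 20-point detectable difference (Sample Size Calculation); cut-off above three (Introduction); sensitivity 93.8% (Abstract, Discussion).

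**Inputs assumed.** Specificity from 0.5 to 0.9, since none is given; true sensitivity of 60% or 70% for a poor score; heavy loss defined as more than 300 ml; the score related to loss only through heavy/not-heavy status; all 200 women pooled with no UAE effect.

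**1. The plan's own figures.** z = (300 − 184)/313 = 0.371, so P(loss > 300 ml) = 35.5% under a normal curve, matching the stated 35%. For 35% v 15%, two-sided 5% and 90% power, the standard two-proportion formula gives 97 per arm (194 in total), and 100 per arm gives 91.0% power. The stated 200 is reproduced. No sample size or precision is stated for the QRS item.

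**2. By hand, what the t-test sees.** Use the normal model.
- Mean loss among heavy bleeders: 184 + 313 × φ(0.371)/0.3555 = 184 + 313 × 0.3725/0.3555 ≈ 512 ml. Among the others: 184 − 313 × 0.3725/0.6445 ≈ 3 ml. The gap is 509 ml.
- Sensitivity 60%, specificity 80%: P(score high) = 0.6 × 0.3555 + 0.2 × 0.6445 = 0.342. Heavy bleeders form 0.2133/0.342 = 62% of the high group and 0.1422/0.658 = 22% of the low group. Expected mean difference ≈ 0.407 × 509 = 207 ml.
- Within-group SD ≈ √(313² − 0.342 × 0.658 × 207²) ≈ 297. SE ≈ 297 × √(1/68.4 + 1/131.6) ≈ 44 ml. The expected t is about 4.7, so p<0.05 is nearly certain although 40% of heavy bleeders are missed.
- Sensitivity 60%, specificity 50%: P(score high) = 0.2133 + 0.3223 = 0.536. Heavy bleeders form 40% and 31% of the two groups. Expected difference ≈ 0.092 × 509 = 47 ml, SE ≈ 44 ml, expected t ≈ 1.1. Here the test usually fails.

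**3. Simulation.** 2000 trials of 200 women per setting, with Student's t-test of blood loss, high v low score. The table shows the share with p<0.05 in the expected direction. Ranges run over lognormal, gamma and normal blood loss with the same mean and SD.

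| Specificity | Sensitivity 70% | Sensitivity 60% |
|---|---|---|
| 0.9 | 99-100% | 98-100% |
| 0.8 | 97-100% | 87-100% |
| 0.7 | 85-99% | 65-90% |
| 0.6 | 65-89% | 36-57% |
| 0.5 | 31-57% | 10-19% |

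A score with true sensitivity of 93.8% gives 95-100% throughout. The Mann-Whitney test gives 83-100% at 60%/80% and 78-100% at 70%/70%, so changing to a rank test does not help.

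**4. What a direct estimate would show.** The trial's own scenario has 35 + 15 = 50 heavy bleeders. The exact 95% intervals for sensitivity are 83.5-98.7% for 47/50, 55.4-82.1% for 35/50 and 45.2-73.6% for 30/50. The last two exclude 93.8%. In the no-UAE arm alone (35 events in 100), 33/35 gives 81-99%. The normal curve behind the 35% also puts 28% of women below zero blood loss. With the same mean and SD, a lognormal puts 16% and a gamma 19% above 300 ml. At 16 events in the no-UAE arm, 15/16 gives 69.8-99.8%.

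**The case against.** The strongest objection is that the document never says how the score will be judged. A reader might infer that p<0.05 on mean blood loss by score group is the validation rule, that 93.8% is the benchmark, and hence that a score missing a third of heavy bleeders would usually count as validated. The text supports none of these steps. No test is tied to the QRS item, the tests are to be used where appropriate, and no pass rule is set. The table above therefore describes a possible reading, not a stated rule. "Usually" also depends on a specificity that the document does not give: it holds at about 0.7 or more, is mixed at 0.6 and fails at 0.5. These limits stand.

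It can also be said that a condensed article may leave accuracy measures to a fuller document. That would answer silence. Here the section is not silent: it prescribes mean and SD for all data and names two tests. The qualifier most naturally governs the choice between them, and both compare means.

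Two objections bear on the remedy, and both stand. The score's target in Table 1 is the need for compression hemostasis, so the 93.8% may not refer to loss above 300 ml. Pooling the arms also ignores that UAE is given to reduce bleeding, so the no-UAE arm is the relevant one. There, a rule requiring an exact lower limit above 70% would be met in only 51% (lognormal), 65% (gamma) or 95% (normal) of trials even if sensitivity were truly 93.8%.

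**Conclusion.** The point holds as a mismatch between a primary outcome and its named analysis: a comparison of means can neither confirm nor refute a sensitivity of 93.8%. This conclusion needs no simulation.

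The size of the possible error is conditional. If a significant mean difference were taken as validation, a score missing 30-40% of women losing more than 300 ml would reach p<0.05 in about 85-99% of trials at 60%/80% or 70%/70%, about 36-89% at specificity 0.6, and about 10-57% at 0.5. These figures rest on assumed sensitivity and specificity, on 300 ml as the event and on pooling the arms. The document should be changed, but it does not commit the trial to a false validation.

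**What to change.** In Primary Outcomes and Statistical Analysis, replace the t-test/ANOVA for the QRS item with a diagnostic-accuracy analysis:

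- At the fixed cut-off (above three), report sensitivity, specificity and negative predictive value with exact 95% confidence intervals, plus the AUC of the 0-6 score.
- State the reference event, and reconcile the need for compression hemostasis in Table 1 with the blood-loss threshold of 300 ml in the sample size section.
- Report by arm, with the no-UAE arm as the main validation set, because the intended use is deciding who can go without UAE.
- Base conclusions on the estimates and intervals, not on p<0.05 for a mean difference. Any numerical success limit should be set in advance by the sponsor. A lower limit of 70% is only an example: it is close to the exact lower limit of 69.8% that would apply if the earlier 93.8% was 15 of 16 events, which is an assumption.

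The cost is a few lines of text and analysis. The score and the blood loss are already to be recorded, though if compression hemostasis is kept as the event, its recording should be confirmed. The downside is that validation becomes harder to claim and the sensitivity interval is wide in the no-UAE arm: 81-99% for 33/35, and wider if fewer than 35% lose more than 300 ml.

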## Discussion

Interventions for cesarean scar pregnancy could cause a massive intraoperative blood loss due to the highly vascular nature of the site of pregnancy. This consequently results in using UAE as one of the options to prevent intraoperative blood loss in clinical practice. However, a recent retrospective study suggested that UAE may be overused in clinical practice (11). Therefore, in this randomized clinical trial, we primarily aim to evaluate the necessity of UAE as a treatment option for cesarean scar pregnancy in order to control the intraoperative blood loss. We will then retrospectively take into account the subtypes of cesarean scar pregnancy to understand whether the optimal options are dependent on the subtypes of cesarean scar pregnancy.

Pre-assessment on predicting intraoperative blood loss which may be dependent on the size and/or site of the sac and the gestational age will help gynecologists select an optimal option for cesarean scar pregnancy treatment. A recent retrospective study used crossover sign (COS) to predict blood loss in surgical treatment (17), suggesting that the crossover sign (COS) is an independent risk factor for severe blood loss during treatment of cesarean scar pregnancy (18). We also recently developed a risk-scoring system (QRS) to estimate blood loss during surgical treatment with a 93.8% sensitivity and 6.3% false negative (13), which has some similarities with the COS system. Due to the relatively small sample size in our previous study, therefore, in this randomized clinical trial with a relatively large sample size, we will retrospectively validate the role of the QRS score in estimating intraoperative blood loss. We hope that this study will generate sufficient evidence for optimal cesarean scar pregnancy treatment. If effective, we believe the QRS score can be a cost-effective and safe tool to estimate intraoperative blood loss in order to reduce the unnecessary use of UAE in clinical practice.

In addition, whether recurrent cesarean scar pregnancy and the outcomes in a subsequent pregnancy including complications,and subsequent fertility in women treated for cesarean scar pregnancy are associated with their previous treatment has not been described well in literature. We hope that the secondary outcomes of the study can provide some useful information on the outcomes of a subsequent pregnancy.

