**Methods and Analysis:**

We propose undertaking a randomized clinical trial sequentially recruiting 200 patients. All the patients will randomly receive ultrasound guided curettage with or without UAE. Data on the subtypes of cesarean scar pregnancy (Types 1 and II and III) detected by ultrasound will be collected before operation. The score on estimating intraoperative blood loss assessed by our recently developed quantitative risk-scoring system (QRS) will be collected before the operation. We will primarily compare the duration of the operation, intraoperative blood loss, and complications between the two groups. We will also retrospectively analyze the association of subtypes of cesarean scar pregnancy and the options of treatment and validate the QRS score. Outcomes of subsequent pregnancy within the 2-year follow-up will be secondary outcomes.

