## Introduction

Cesarean scar pregnancy is a rare type of ectopic pregnancy implanted in the myometrium at the site of a previous cesarean section scar. Although the estimated incidence is 0.04 to 0.05% of pregnancies worldwide (1), the number of reported cases has significantly increased in the last decade. Given the risk of this life-threatening complication, management of cesarean scar pregnancy is becoming another challenge for gynecologists.

There is currently no agreement on the most optimal management of cesarean scar pregnancy. Lack of clinical trial studies with a large enough sample size to compare the advantages among the treatment options (2, 3) results in the majority of studies on cesarean scar pregnancy being reported in literature as case series (4). This consequently results in that the optimal treatment is likely based on the individual case (4, 5) and the hospital’s individual protocol or gynecologists’ experiences. Although medical treatment with systemic or local methotrexate (MTX) is popular in western countries because of the lower risk for blood loss, nearly 50% of cases diagnosed in the first trimester of pregnancy often receive surgical treatment (1). Surgical treatment includes transvaginal or hysteroscopic or laparoscopic resection and uterine artery embolization (UAE) combined with or without hysteroscopic resection or curettage (4, 6, 7).

Increasing evidence indicated that cesarean scar pregnancy is a precursor of abnormally adherent placenta later in pregnancy (8), suggesting an increased risk of a severe hemorrhage or hysterectomy could occur at the time of operation/delivery (1, 8). Although UAE can reduce the risk of intraoperative blood loss and shorten the time for *β*-hCG (human chorionic gonadotropin) normalization and hospital stay and is a safe option for caesarean scar pregnancy treatment (9, 10), a recent retrospective study reported that the necessity of UAE is low (11), suggesting that UAE may be overused in clinical practice, in particular in China (4). A recent retrospective study also reported that simple surgical suction curettage under ultrasound guidance for the treatment of cesarean scar pregnancy in a lower uterine segment is effective and safe with less intraoperative blood loss (12).

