### Intervention

Eligible patients will randomly receive ultrasound guided suction curettage with or without pre-operative UAE treatment (**Figure 1**). If there is an emergency such as severe bleeding or uterine rupture during treatment, the patients will receive hysteroscopic and/or laparoscopic resection.

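### QRS validation is placed in the trial as a whole with no account of arm; if UAE works as the design assumes, pooling both arms would understate the score's specificity and positive predictive value for its stated use

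*Protocol article*

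**What the plan says.** The Primary Outcomes section lists the item "Retrospectively validate the QRS score to predict intraoperative blood loss" and names no arm or subset. The Introduction and the Discussion both place this validation in the trial and point to its size. The Discussion contrasts that size with the small earlier study: "with a relatively large sample size, we will retrospectively validate the role of the QRS score in estimating intraoperative blood loss". The only sample size given for the trial is in Sample Size Calculation: "200 women newly diagnosed with cesarean scar pregnancy will be recruited within three years and equally divided into two groups".

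The order of events is also fixed. According to the abstract, the score "assessed by our recently developed quantitative risk-scoring system (QRS) will be collected before the operation". Under Intervention, "Eligible patients will randomly receive ultrasound guided suction curettage with or without pre-operative UAE treatment". In the UAE arm, embolization therefore comes before blood loss is measured, and the score reflects the woman's risk before surgery.

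On what UAE does, the Introduction states that "UAE can reduce the risk of intraoperative blood loss", and the Discussion describes "using UAE as one of the options to prevent intraoperative blood loss in clinical practice". On what the score is for, the Discussion hopes for a tool to "estimate intraoperative blood loss in order to reduce the unnecessary use of UAE in clinical practice". The Statistical Analysis section names only the t-test and ANOVA and does not describe the validation.

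**The concern.** A score used to decide who can do without UAE has to predict what happens without UAE. Only the curettage-only arm shows that directly. In the UAE arm, a woman who was rightly flagged, but whose bleeding UAE then prevented, is counted as a false alarm. If the arms are combined with no account of treatment, the better UAE works, the less specific the score appears and the lower its positive predictive value (PPV).

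The validation is a listed primary outcome and is tied to a practical claim about sparing women UAE. Accuracy figures that mix treated and untreated women would misstate how many flagged women would in fact bleed without UAE. The randomized comparison of the arms is not affected.

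**Working it through.** **Inputs from the article.** 200 women, 100 per arm; mean blood loss 184 ml, SD 313 ml; about 35% above 300 ml; a 20-point difference, described as a reduction, hence 35% to 15%; 90% power, two-sided 5%; QRS sensitivity 93.8%; risk cut-off above 3.

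**Assumptions, not in the article.** Specificity without UAE is 70 to 90%. The 93.8% applies to loss above 300 ml in women without UAE. The 35% is the rate without UAE.

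**The plan's own figures reproduce.** 1 − Φ((300 − 184)/313) = 35.5%, against the stated 35% or so. For 35% versus 15% at 90% power, the two-proportion formula gives 97 per arm (194 in total), and 100 per arm gives 91.0% power. The planned 200 is consistent with the planned effect.

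**No-UAE arm, per 100 women, specificity 80%.**
- Bleeders: 35, of whom 0.938 × 35 = 32.83 score above 3 and 2.17 do not.
- Non-bleeders: 65, of whom 0.20 × 65 = 13 score above 3 and 52 do not.
- PPV = 32.83 / (32.83 + 13) = 71.6%.

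**UAE arm, per 100 women.** Randomization gives the same expected score distribution (45.83 above 3, 54.17 not), but 15 bleeders. Two patterns of UAE effect are considered.
- *Proportional at all scores* (relative risk 15/35 = 0.4286): bleeders above 3 = 32.83 × 0.4286 = 14.07; bleeders not above 3 = 0.93.
- *Benefit only in women scoring above 3*: bleeders not above 3 stay at 2.17; bleeders above 3 = 15 − 2.17 = 12.83.

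**Pooled, 200 women: 50 bleeders, 150 non-bleeders, 91.66 scoring above 3.**
- *Proportional*: PPV = (32.83 + 14.07)/91.66 = 51.2%; specificity = (52 + 53.24)/150 = 70.2%; sensitivity = 46.90/50 = 93.8%.
- *High scorers only*: PPV = (32.83 + 12.83)/91.66 = 49.8%; specificity = (52 + 52)/150 = 69.3%; sensitivity = 45.66/50 = 91.3%.

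**Across the assumed specificities:**

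| Specificity without UAE | PPV without UAE | Pooled specificity (proportional / high scorers only) | Pooled PPV (proportional / high scorers only) |
|---|---|---|---|
| 70% | 62.7% | 61.5% / 60.7% | 44.8% / 43.6% |
| 80% | 71.6% | 70.2% / 69.3% | 51.2% / 49.8% |
| 90% | 83.5% | 78.8% / 78.0% | 59.6% / 58.0% |

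Specificity falls by about 9 to 12 points and PPV by about 18 to 25. Negative predictive value hardly moves: at 80% specificity it goes from 96.0% to 97.1% in the proportional case and is unchanged in the other.

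**Dependence on the UAE effect.** In the proportional case, pooled PPV = PPV without UAE × (1 + RR)/2. At RR = 0.4286 the factor is 0.714. At RR = 1 it is 1, so there is no distortion.

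**Precision.** Half-width = 1.96 × √(0.938 × 0.062 / events): 8.0 points with 35 events (no-UAE arm), 6.7 with 50 (pooled). Exact 95% intervals are about 81 to 99% for 33/35 and 83 to 99% for 47/50.

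**The case against.** The strongest objection is that pooling is nowhere stated. The text speaks of the trial and its size; it does not say that both arms will be combined. The size of the earlier study is not given, so 100 women might also count as relatively large beside it. The analysis plan and full protocol are not shown and may specify validation by arm. This stands in part. A reader might infer that the protocol commits to an unadjusted pooled accuracy figure, and the document does not support that. It does support something narrower: a primary outcome with no arm named, justified by the size of a trial whose only stated size is 200. That rationale is open to challenge even without an analysis plan.

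A second objection is that the bias is conditional. The trial asks whether UAE is overused, and if UAE has no effect, pooled and no-UAE accuracy coincide. This is correct. A reader might also infer that every accuracy measure would be wrong. That does not follow: sensitivity, the only performance measure that the article reports (with its complement, the false-negative rate), is unchanged under a proportional effect and moves 2.5 points otherwise.

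Third, the sizes rest on inputs from outside the article. Specificity is not reported. Nothing says that the women in the development study had no UAE. Table 1 is titled for the need for compression hemostasis, which may not be the same endpoint as loss above 300 ml. All of this stands, so the figures are illustrations and not predictions.

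Finally, restricting to one arm is not the only sound approach. A model on all 200 women with treatment and a score-by-treatment term is also valid.

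**Conclusion.** The concern holds in conditional form. As written, the validation is placed in the whole trial because of its size and takes no account of a treatment that intervenes between score and outcome. For the score's stated use, the relevant accuracy is that in women without UAE.

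Under the design's own effect (35% to 15%) and the assumptions listed in the working, an unadjusted pooled analysis would understate specificity by about 9 to 12 points and PPV by about 18 to 25. Sensitivity would stay at 93.8% or fall to about 91%. A smaller UAE effect gives a smaller distortion, and no effect gives none. It would go too far to say that the protocol has fixed a wrong analysis: pooling is the natural reading of the text but is not literally there. The point is worth correcting because the validation is a primary outcome and the correction is cheap.

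**What to change.** In Primary Outcomes, state that the main QRS validation (cut-off above 3) is done in the curettage-only arm, and that results in the UAE arm are reported separately. Add that any analysis of all 200 women will include treatment and a score-by-treatment term, and that no unadjusted pooled accuracy figure will be given. Change the references to sample size in the Introduction and Discussion to match.

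The change is to wording only; sample size, randomization and data collection stay as they are. The price is precision: at the plan's rates, about 35 events instead of 50, so the 95% half-width for sensitivity is about 8.0 points instead of 6.7.
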